#### Methods in analysis to handle protocol non-adherence and any statistical methods to handle missing data

The primary analysis population will include all enrolled participants, regardless of protocol adherence, following the intention-to-treat principle. For participants who discontinue or deviate from the protocol, available outcome data will still be collected and included in the analysis to minimize attrition bias. For each specific feasibility outcome, it will be counted as a success if it was known to happen and a failure if either it was known to not happen or its status is unknown.

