**Methods:**

This two-site single-arm feasibility trial aims to enroll neonates with presumed simple gastroschisis over 30 months. The intervention has two main components: Replogle suction tube removal within 24 h of abdominal closure and starting small-volume human milk feeds within 48 h of abdominal closure. Feeding volume will be advanced as tolerated, following the University of California Fetal Consortium pathway, which is standard care. Feasibility outcomes include enrollment rate, protocol adherence, fidelity, and withdrawal rate. Exploratory outcomes include hospitalization length, time to full feeds, duration of parenteral nutrition, use of human milk, breastfeeding rates, and anthropometric measurements. Safety measures involve monitoring for feeding-related complications, infections, and unexpected surgical interventions.

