### Outcomes

#### Feasibility objective outcomes

We will test the feasibility of implementing an early feeding protocol for neonates with gastroschisis. Feasibility will be assessed through:Objective 1 Enrollment (primary feasibility objective): obtain consent from ≥ 80% of eligible neonates’ parents/guardians from the prenatal period to within the first 24 h of abdominal closure.Objective 2 Protocol adherence: ≥ 85% of enrolled neonates receive introductory feeds within 48 h of abdominal closure.Objective 3 Fidelity: feeding protocol adherence with ≥ 90% of predefined protocol steps.Objective 4 Withdrawal: < 10% of enrolled neonates withdraw.

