### Sample size

We plan to enroll 20 neonates with gastroschisis from the University of California Davis (UCD) and the University of California Los Angeles (UCLA). This sample size was determined based on availability and feasibility. We estimate that approximately 10 neonates per year will meet the eligibility criteria, yielding a denominator of approximately 40 for the consent outcome (feasibility objective 1) and that the number of enrolled patients will be at least 20 for the proportions used for feasibility objectives 2 to 4. These two denominators will allow us to estimate these proportions with error margins less than 16 and 22 percentage points, respectively.

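### The missing-data rule for feasibility outcomes suits favourable events; taken literally it counts infants of unknown status as not withdrawn under objective 4 (minor)

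*Protocol article*

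**What the plan says.** The rule is in the protocol article, in the section on protocol non-adherence and missing data under Statistical methods. Its scope is general and names no exception: "For each specific feasibility outcome, it will be counted as". The coding that follows is "a success if it was known to happen and a failure if either it was known to not happen or its status is unknown". The same section keeps all enrolled infants in the primary analysis population, whether or not they adhered.

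Withdrawal falls within that scope. The Methods part of the abstract states: "Feasibility outcomes include enrollment rate, protocol adherence, fidelity, and withdrawal rate". Under Feasibility objective outcomes, objective 4 reads: "Withdrawal: < 10% of enrolled neonates withdraw".

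The other three objectives run the opposite way. Objective 2, for example, is "≥ 85% of enrolled neonates receive introductory feeds within 48 h of abdominal closure". Objectives 1 and 3 likewise set lower limits, of 80% and 90%, on something desirable.

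The article gives no separate rule for objective 4 and does not restate it as retention.

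**The concern.** Counting unknown as failure is meant to be a cautious convention: lost information should not help a trial reach its target. That works when the event is the desired one. For objective 4 the event that may or may not be known to happen is withdrawal. On the words as they stand, a known withdrawal is labelled a success, and an infant of unknown status is put with those known not to have withdrawn. Missing status can then only lower the withdrawal proportion or leave it unchanged. One rule is therefore cautious for three objectives and lenient for the fourth.

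At stake is whether the under-10% target is reported as met. With about 20 infants, one or two of them settle that.

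**Working it through.** **Inputs**

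- Denominator for objectives 2 to 4, from Sample size: "the number of enrolled patients will be at least 20 for the proportions used for feasibility objectives 2 to 4". I take n = 20.
- Target for objective 4: fewer than 10% withdraw.
- Unknowns stay in the denominator, because all enrolled infants are analysed.

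**The plan's own precision figures.** The worst-case 95% half-width is 1.96 × √(0.25/n). For n = 40 it is 15.5 points, and for n = 20 it is 21.9 points. The stated limits of 16 and 22 points reproduce and are not in dispute.

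**What the target allows.** At n = 20, 1/20 = 5% meets it and 2/20 = 10% does not, so at most 1 withdrawal is allowed.

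**Two codings.** Let w be known withdrawals and u infants of unknown status. The literal rule gives w/n. Counting unknown as withdrawn gives (w + u)/n. The first can never exceed the second.

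| w | u | Literal rule | Unknown = withdrawn |
|---|---|---|---|
| 0 | 1 | 0% (met) | 5% (met) |
| 0 | 2 | 0% (met) | 10% (not met) |
| 1 | 0 | 5% (met) | 5% (met) |
| 1 | 1 | 5% (met) | 10% (not met) |
| 1 | 2 | 5% (met) | 15% (not met) |
| 2 | 0 | 10% (not met) | 10% (not met) |

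The conclusion changes with one unknown if there is one known withdrawal, and with two unknowns if there is none. It does not change when nothing is unknown, or when two or more withdrawals are known.

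**Illustration under assumed rates.** The article gives no withdrawal rate and no rate of unknown status. Suppose a true withdrawal probability p, with a share m of true withdrawals left at unknown status. The chance of meeting the target is P(X ≤ 1) = (1 − q)^20 + 20q(1 − q)^19, with q = p(1 − m) under the literal rule and q = p if unknowns count as withdrawn.

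| p | Literal, m = 25% | Literal, m = 50% | Unknown = withdrawn |
|---|---|---|---|
| 10% | 0.55 | 0.74 | 0.39 |
| 15% | 0.33 | 0.55 | 0.18 |

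These values of m show direction and scale only. They are not a forecast and are probably high for this setting.

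**The case against.** **The intended meaning may be retention.** The authors surely did not mean withdrawal to be a success. The natural success for an infant under objective 4 is not withdrawing, and on that reading an unknown already counts against the target. This stands in part: a reader might infer that the rule is definitely inverted in intent, and the article does not support that. But the objective is worded in terms of the share "of enrolled neonates withdraw", and the rule turns on what is known to happen, so the text does not state the retention reading either. A clarifying sentence is needed in both cases.

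**Unknown status should be rare.** This largely stands. The infants are inpatients, data come from the health record through initial discharge, withdrawal rates are tracked (Plans for assessment and collection of outcomes), and key data are still sought after a family discontinues or deviates. A reader might infer that infants lost from view have in effect withdrawn, so that the trial is likely to report good retention wrongly. Nothing in the article supports that.

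**Little depends on it.** This also stands. Objective 1 is the primary feasibility objective, no efficacy hypothesis is tested, and the text shown ties no decision to proceed to the 10% limit. Results will carry 95% intervals, and the exact intervals for 1/20 (about 0.1% to 25%) and 3/20 (about 3% to 38%) both contain 10%. The met or not-met statement can change while the statistical message about retention changes little.

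**The analysis plan may settle it.** It may. But the published rule covers each feasibility outcome, so a plan that coded withdrawal differently would contradict it, and this section would still need correcting.

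**Conclusion.** The point holds as a minor error of wording in a stated rule. Read literally, the rule is conservative for objectives 1 to 3 and anti-conservative for objective 4. In the smallest case that matters, one known withdrawal and one unknown among 20 infants, the reported rate is 5% (met) as written and 10% (not met) under the cautious coding.

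This rests on two assumptions: exactly 20 infants are enrolled, and at least one has unknown withdrawal status. At n = 21, for instance, two withdrawals would be 2/21 = 9.5% and would meet the target, so the tipping count shifts with enrolment. If every infant's status is known, the two codings agree on the withdrawal rate and only the success label is wrong. The sample size, the stated error margins and the primary feasibility objective are unaffected.

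**What to change.** Add to the section on non-adherence and missing data that, for objective 4:

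- success means the infant is known not to have withdrawn;
- unknown withdrawal status counts as withdrawn;
- an infant who dies in hospital without having been withdrawn is not counted as a withdrawal.

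Leave the rule for objectives 1 to 3 unchanged.

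The third item is needed because the article lists mortality among its adverse event outcomes. If success were instead defined as remaining in the study until discharge, an in-hospital death would fail it, and with only 1 withdrawal allowed in 20 that could decide the result.

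The cost is a sentence or two of text, and the reported withdrawal rate may be slightly higher. Recruitment has begun and a feasibility review is planned at the midpoint of enrolment, so the coding is best settled before that review.

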#### Adverse event reporting and harms

Potential adverse events will be discussed and categorized (based on severity, expectedness and relatedness) by the principal investigators.

## Discussion

This prospective study of a standardized feeding protocol for neonates with gastroschisis faces several operational challenges. Recruitment may be limited by the rarity of the condition and the need to approach families during a stressful time. To address this, we have streamlined screening and consent processes and provided targeted staff education.

Coordinating data collection across two centers requires clear communication and standardized procedures. Regular joint meetings and routine data audits are in place to ensure data quality. Protocol adherence is promoted through staff training, site champions, and visual reminders.

Given the vulnerable neonatal population, all protocol changes receive IRB approval and participant safety is closely monitored. While the sample size and single-region setting may limit generalizability, the study will provide valuable insights into feeding management for neonates with gastroschisis and inform future research.

## Trial status

IRB Protocol Version Date is January 31, 2025. Recruitment started February 20, 2025. The anticipated date of recruitment completion is February 1, 2028. Registered March 10, 2025 retrospectively registered.

## Data Availability

After publication, de-identified participant data will be available to qualified researchers upon request, subject to a data-use agreement, study team review, and IRB approval. Access will be granted within 12 months for requests meeting scientific and ethical standards.

## Abbreviations

NICU: Neonatal intensive care unit
UCD: University of California Davis
UCLA: University of California Los Angeles
UCfC: University of California Fetal Consortium
PN: Parenteral Nutrition
DMC: Data Monitoring Committee
EMR: Electronic Medical Record
GCP: General Clinical Practice
